# 0. overview

## Shema

　The groups will be divided according to eligibility criteria and other factors based on the following two shema.

Main eligibility criteria: students of our University's Department of Health Sciences

Registration and allocation

Target number of registered participants: 60

　　Enrolment period: from the date of Ethics Committee approval to 31 January 2024

Group M (20 participants, massage)

(Intervention by exercise stimulus)

Effectiveness assessment: measuring each indicator before and immediately after the intervention

Group C (20 participants, control)

Group P (20 participants, physical stimulation)

## Purpose and significance

　The aim of this study was to examine whether exercise and physical stimulation interventions on the tissues around the knee joint can change the flexibility and gliding properties of the tissues in healthy subjects, using ultrasound imaging equipment.

　If the usefulness of the intervention is confirmed through this study, it will provide a basis for the development of new medical technology and contribute to the development of rehabilitation medicine.

## Target

Students of our University's Faculty of Medicine

## Target number of people to be enrolled and duration of study

　Target number of patients enrolled: 60 (20 in group M, 20 in group P and 20 in group C)

　Enrolment period: from the date of Ethics Committee approval to 31 January 2024, depending on the subject.

　　Duration of the study: from the date of approval by the Ethics Committee to 31 March 2024

## Research design

　□Study design: randomised controlled trial in a parallel design

　□Type of control: no intervention

　□Randomisation: stratified block randomisation method

　□Level of blinding: unblinded

## Assessment items

　　Main endpoints: ultrasound imaging (flexibility of the fat body under the patella, gliding of the medial patellar girdle)

　　Secondary endpoint: other ultrasound imaging data

# 1. purpose and significance

There have been reports on subjective methods of assessing the gliding properties of periprosthetic tissues in the knee joint using ultrasound imaging, but no objective methods have been devised to date.

The purpose of this study was to quantitatively examine whether exercise and physical stimulation of the tissues surrounding the knee joint can change the flexibility and gliding ability of the tissues using ultrasound imaging in healthy subjects. Specifically, we will target the knee joint, which is prone to contracture (restriction of joint movement) in many diseases, and quantitatively evaluate (1) the flexibility of the infrapatellar fat pad and (2) the gliding of the medial patellar band due to contraction of the vastus medialis muscle, and examine the changes before and after intervention.

　If the usefulness of the intervention is confirmed through this study, it will provide a basis for the development of new medical technology and contribute to the development of rehabilitation medicine.

# 2. background and rationale

　Skeletal muscles and their tendons are the main tissues responsible for the movement of joints in the human body and are one of the many soft tissues that span joints throughout the body. The skeletal muscles and their tendons are one of the many soft tissues that span the joints of the body. While the normal elasticity, flexibility and gliding properties of the skeletal muscles and their tendons do not interfere with joint movement, prolonged periods of rest and bed rest associated with hospitalization and treatment for diseases and other conditions often result in a decline in their function and contractures. In particular, in elderly patients, the proportion of which is increasing significantly in Japan, the early release from bed, smooth return to home and quality of life are adversely affected. Therefore, it is desirable to take appropriate measures to prevent and treat contractures from the early stages of treatment, but the detailed pathogenesis remains unclear and there is no evidence-based treatment or therapy. Although it has been reported that the cause of contractures is largely due to a decrease in muscle-tendon elasticity, flexibility and gliding, previous research by the applicant suggests that degeneration of the fatty tissue surrounding the knee joint also contributes to contractures and dysfunction ([name] et al, J Med Ultrason 2019, etc.). However, based on the findings of other relevant previous studies, the detailed pathogenesis of contractures remains unclear.

In Japan, where the population is aging, it is one of the most urgent issues from the perspective of extending healthy life expectancy and controlling soaring medical costs to return patients whose physical functions deteriorate due to hospitalization for diseases to society in good health as much as possible (Ministry of Health, Labour and Welfare, Japan, 2018). We have analyzed studies on the early discharge of hospitalized patients, their return to home, and the improvement of their quality of life from various perspectives. We have also found that ultrasound findings of knee joint components are associated with various physical functions ([name] at al., in press). The aim of this study is to examine the usefulness of physiotherapeutic approaches to the flexibility and gliding of the anterior and medial knee joint surrounding tissues, which tend to cause pain in clinically limited range of motion of the knee joint.

# 3. overview of the test drug

　This is a drug-free study. The aim of this study is to compare the changes in the dynamics of the tissues around the knee joint using ultrasound imaging, before and after intervention, in order to develop a new physiotherapeutic treatment.

# 4. eligibility criteria

Eligible students of the University's Faculty of Medicine who meet all of the following selection criteria and none of the exclusion criteria are eligible for enrolment.

## 4.1 Selection criteria

　Minors are also included because it is necessary to include them in order to ensure the sample size necessary to carry out this study.

A student of the University

　A person who is 18 years of age or older at the time the consent form is obtained.

　(3) Those who have given written consent based on the subject's own free will after receiving sufficient explanation for participation in this study.

　We will recruit students by posting notices on campus noticeboards and by other means.

## 4.2 Exclusion criteria

　　(i) Those with sensory impairment in the lower limbs

　　(2) Patients with a history of neurological or orthopaedic disease of the spine or lower limbs

　　(3) Any other person who is judged by the principal investigator to be unsuitable as a human subject.

　Those with limited knee extension or hypermobility for any reason.

## 4.3 Subjects for whom consent by a substitute is required and the reasons for this

　Considering the age structure of the subjects of this study, minors are also included because it would be difficult to carry out this study without including them.

　Consent shall be obtained from a surrogate when conducting research on the above subjects. The substitute will be selected from those who are considered to be able to represent the subject's wishes and interests, taking into account the subject's family structure. Persons who are considered appropriate as surrogates are listed below.

Parent of the subject

Spouse of the subject

Adult child

Adult siblings or grandchildren

Grandparents

Adult relatives or persons considered to be equivalent to these relatives

# 5. research methods

## 5.1 Research design

　□Study design: randomised controlled trial in a parallel design

　□Type of control: no intervention

　□Randomisation: stratified block randomisation method

　□Level of blinding: unblinded

## 5.2 Outline of the study

Massage and exercise group (group M), physical stimulation group (group P)

Register

Eligibility check

Obtaining consent

Intervention period

Pre-observation period

Tracking period

One single intervention

None in particular

2 weeks

End of experiment

End of intervention

Start of intervention

Control group (Group C)

The pre-observation period, intervention period and follow-up period all follow the same process as above.

No intervention, but a total of two ultrasound imaging sessions with a 10-minute pause for comparison with the intervention group.

## 5.3 How interventions are delivered

Exercise stimulus group; 1/3 of participants

　A massage/manual therapy, quantified in a preliminary experiment, will be performed on the infrapatellar fat pad for approximately 10 minutes. Specifically, a pressure sensor will be used to measure the finger pressure during the manual approach of the interventionist to ensure that a constant pressure is applied.

[figure not shown]
　　　　　
[figure not shown]

Physical stimulus group; 1/3 of participants

　The infrapatellar fat pad body is subjected to vibration stimulation quantified in the preliminary experiment for approximately 10 minutes. The frequency of the vibration stimulation is quantified by using a device that can quantify the frequency of the vibration stimulation, so that the vibration stimulation is applied at a constant frequency.

Equipment to be used: Slieve MD01 handy massager.

The interventions in the above two groups will be carried out by a researcher ([name]) who has been carefully trained beforehand.

Control group; 1/3 of participants

　No specific interventions will be made, but there will be a 10-minute waiting period.

## 5.4 Provisions for concomitant medicines (combination therapy)

Not applicable.

## 5.5 What to do with subjects after completion of the study

　After the completion of this study, the principal investigator will provide the subjects with a summary of the information, including the results obtained in this study, which may be of benefit to medical education.

# 6. method of registration and allocation of subjects

##

## 6.1 Registration of subjects

　The principal investigator or sub-investigator (hereafter referred to as the "principal investigator") will complete the Subject Registration Form and submit it to the Data Management Officer. The data management officer will review the eligibility and notify the researcher in writing of the result of the decision. The researcher registers the subject, attaching the result of the Data Management Officer's decision to the Subject Registration Form.

## 6.2 Allocation method and allocation adjustment factors

　If, in a preliminary experiment, factors are identified that clearly influence the outcome (e.g. gender), then stratified block randomisation by these factors will be used. No pre-allocation adjustment factors will be assumed, as previous studies have shown that absence of a clear history of acute trauma or knee disease is unlikely to affect outcome.

7. endpoints

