# 8. observations and tests

Observation, examination and reporting schedule (Group M, Group P, Group C)

| Occasion  Inspection, observation and investigation items | Pre | Before | After |
| --- | --- | --- | --- |
|  |  |  |  |
| Obtaining consent | ● |  |  |
| Subject background (age, medical history) | ● |  |  |
| Physical examination (height and weight) | ● |  |  |
| Ultrasound images |  | ● | ● |
| Adverse events | ←△→ | | |

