# 11. statistical matters

## 11.1 Basis for setting the target number of people to be registered

To examine the changes before and after the intervention between the three different groups. The rationale for the number of subjects in each group will be based on sample size calculations. Specifically, a two-way analysis of variance will be used for statistical analysis. The number of levels is 1 (before or after the intervention) and the number of groups is 3. Assuming an effect size of 0.4, a significance level of less than 5% and a power of 0.8, the sample size for each group will be calculated to be 52 participants in total. Assuming that there will be a certain number of subjects who declare that they cannot consent to randomisation and who meet the exclusion criteria, we aim to enroll 60 subjects.

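### Sections 0 and 5.1 fix stratified block randomisation, section 6.2 makes it conditional with no factor and no fallback, and the stated analysis has no term for a stratum if one is used

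*Protocol*

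**What the plan says.** Protocol, overview (Research design) and section 5.1: "Randomisation: stratified block randomisation method". Neither place names a factor or attaches a condition.

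Protocol, section 6.2, sets a condition: "If, in a preliminary experiment, factors are identified that clearly influence the outcome (e.g. gender"), "then stratified block randomisation by these factors will be used". It continues: "No pre-allocation adjustment factors will be assumed". The reason given is that, without a clear history of acute trauma or knee disease, such factors are unlikely to affect the outcome. The section does not say which scheme applies if the preliminary experiment identifies nothing.

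Protocol, section 11.1: "a two-way analysis of variance will be used for statistical analysis", with before/after and group as the two factors. Section 11.3.2 compares the mean of each index between the three groups and bases its usefulness rule on means after the intervention. Neither section mentions a stratum. Section 11.3 describes itself as a summary and leaves the details to a statistical analysis plan due before first enrolment.

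Protocol, section 8, schedule: "Subject background (age, medical history"), plus height and weight. Sex is not on the schedule, but section 11.3.1 lists it among the background data to be obtained.

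**The concern.** The allocation list must exist before the first subject is randomised, so the method has to be settled by then. Two places state it as settled. The section meant to define it leaves it open, with a default of no factor. Stratified allocation without a factor has no content beyond ordinary blocking, and the protocol does not say that ordinary blocking is what it means.

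The reason given in 6.2 concerns trauma and knee disease. It does not bear on gender, the one example the section offers.

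The analysis point follows from this. A factor would enter the randomisation only because it clearly influences the outcome. Balancing the arms on such a factor and then leaving it out of the model keeps its variance in the error term, while the design has removed it from the differences between groups. The test is then conservative, and the precision gained by stratifying is not used.

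**Working it through.** **1. The text side by side.** Overview and 5.1: stratified, unconditional, no factor. 6.2: stratified if a factor is found, otherwise no factor, no alternative scheme. These agree only if a factor is found, and the protocol does not report that one was. Section 5.3 treats the interventions as already quantified in a preliminary experiment, while 6.2 still leaves open whether a preliminary experiment identified a factor.

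**2. The plan's own sample size.** Inputs from 11.1: "Assuming an effect size of 0.4, a significance level of less than 5% and a power of 0.8"; "The number of levels is 1 (before or after the intervention) and the number of groups is 3". Reading 0.4 as Cohen's f (an assumption), the power is that of a noncentral F test with λ = f²N. With numerator df = 1 and N = 52, λ = 0.16 × 52 = 8.32, denominator df = 49 and power = 0.807. N = 51 gives 0.799, so 52 is reproduced. The same test at N = 60 has power 0.861. A comparison of three groups has 2 df. At N = 60, λ = 9.6, denominator df = 57 and power is 0.776. The 2-df figure is the baseline below. The gap between 1 and 2 df is a separate matter from this point.

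**3. Cost of a stratum term.** One binary factor takes 1 df. If it predicts nothing, power at N = 60 goes from 0.7757 to 0.7753 (2 df), or from 0.8612 to 0.8610 (1 df).

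**4. After-values compared, stratum explaining a share R² of outcome variance.** R² is assumed; the documents give no value. Adjusted: f becomes 0.4/√(1−R²), λ = 9.6/(1−R²), denominator df = 56. Unadjusted: simulation with 60 subjects in two equal strata balanced across the three arms.

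| R² | λ adjusted | Power adjusted | Power unadjusted | Type I error unadjusted |
|---|---|---|---|---|
| 10% | 10.67 | 0.820 | about 0.78 | about 0.036 |
| 20% | 12.00 | 0.865 | about 0.78–0.79 | about 0.024 |
| 30% | 13.71 | 0.908 | about 0.79 | about 0.014 |

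The type I errors come from 2 million draws. Smaller simulations gave 0.034–0.037, 0.024–0.025 and 0.013–0.014. With the stratum in the model, type I error is about 0.05.

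**5. Change, or after-values adjusted for the before value.** A factor that shifts the level equally before and after cancels in the change. Simulated type I error without the stratum is about 0.05, and the term adds no power. With the before value as covariate and f = 0.4 on the adjusted residual scale, suppose the factor explains 20% of the level at both times. Adding it raises power from 77.5% to 79.4% at a before–after correlation of 0.7, and to 78.7% at 0.8. With 10% explained and correlation 0.7 the gain is under 1 point. The gain is larger for a weaker correlation or a stronger factor: about 3 points in simulation at 20% and 0.5, and also at 30% and 0.7; about 6 points at 30% and 0.5.

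**6. Chance imbalance in sex without stratification.** Assume 50% women and 20 per arm. For two given arms, the difference in counts plus 20 is Bin(40, 0.5), so P(difference ≥ 4) = 2 × P(Bin(40, 0.5) ≥ 24) = 0.268.

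**The case against.** The strongest reply is that 6.2 is the operative section and the other two entries are one-line labels. If no factor is found, the scheme reduces to block randomisation in a single stratum. Model terms may properly be left to the statistical analysis plan, and a factor not yet identified cannot be named. Much of this stands. The randomisation can still be carried out. The missing model term is a consequence of the unsettled allocation, not a separate omission. What remains is that the protocol says stratified twice without condition and never states the fallback.

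Four stronger readings are tempting and are not supported.

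- A reader might infer that the trial loses 4 to 12 points of planned power. Unadjusted power after stratifying is about 0.78–0.79, no lower than the 0.776 baseline, so adjustment is a possible gain. The large gain also needs an analysis of after-values alone. Section 11.1 points to a before/after-by-group test, in which a level effect cancels.
- A reader might infer that sex has to be the stratum. Section 6.2 gives gender only as an example, and no sex effect on these ultrasound indices is shown.
- A reader might infer that sex is not recorded. Section 11.3.1 lists it; only the section 8 row is incomplete.
- A reader might take the 27% imbalance as bias. It is chance imbalance, which the test's error rate already covers, and so a matter of precision.

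**Conclusion.** The contradiction between the overview, 5.1 and 6.2 is real and should be settled before the allocation list is made. It does not invalidate the trial.

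The analysis consequence is conditional: it arises only if a factor is used. Sections 11.1 and 11.3.2 do not settle whether after-values or changes carry the primary test, and the size depends on that. For after-values alone, the test is conservative at the levels in the table and the term could add about 4, 8 or 12 points of power. For change or baseline-adjusted values the gain is about 0 to 2 points under the 10–20% and 0.7–0.8 assumptions.

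All of these figures assume Cohen's f = 0.4, 60 subjects analysed, two equal strata, a 2-df test and the chosen share of variance explained. None of those shares comes from the documents. If the factor has no prognostic value, the gain is nil.

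**What to change.** Before first enrolment:

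1. Make sections 0, 5.1 and 6.2 agree. Either name the factor or factors found in the preliminary experiment and stratify the blocks by them, or replace stratified with unstratified permuted blocks in all three places.
2. State the primary comparison as after-values between groups adjusted for the before value, which is already collected. Include every factor used to stratify as a model term. The protocol can say this in one sentence and leave the detail to the statistical analysis plan.
3. If sex is the factor, add it to the pre-visit background row in section 8, in line with 11.3.1, so that it is known before allocation.

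Cost: rewording three short entries and one analysis sentence, 1 df per binary factor (power falls by less than 0.001 if the factor is useless), and one allocation list per stratum if stratification is kept. No extra subjects or measurements are needed.

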## 7.1 Primary endpoints

　　Main endpoints: flexibility of the fat body under the patella calculated using ultrasound images and gliding of the medial patellar strut with contraction of the vastus medialis

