## 11.3 Analysis items and methods

　A summary of the statistical analysis is given below. The significance level of the test is set at two-sided 0.05. For details, [name], who is responsible for the statistical analysis, will prepare the first version of the statistical analysis plan before the first patient is enrolled (first patient in), and if necessary, the second version will be fixed before the data are fixed. If a second version is prepared, it will include a history of changes from the first version.

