### 11.3.2 Hypothesis-testing analysis of primary endpoints

To determine and compare the effects on the tissues surrounding the knee joint before and after the intervention, we will compare the average of each index between the three groups.

If the p-value of this test is less than 0.05 and the mean value of each indicator after the intervention is higher in group M or P than in group C, we judge that the intervention may be useful.

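### Two primary endpoints share one unadjusted 0.05 level, and the success rule in 11.3.2 does not say whether one or both must be significant

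*Protocol*

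**What the plan says.** - Protocol 7.1 defines the main endpoints as "flexibility of the fat body under the patella calculated using ultrasound images and gliding of the medial patellar strut" with contraction of the vastus medialis. The overview (assessment items) lists the same two, and section 1 presents them as two numbered aims of equal standing.
- Protocol 11.3: "The significance level of the test is set at two-sided 0.05". No split, order or co-primary rule is given.
- Protocol 11.3.2 says of the analysis that "we will compare the average of each index between the three groups". The decision rule has two parts: a test condition, "If the p-value of this test is less than 0.05", and a direction condition, "the mean value of each indicator after the intervention is higher in group M or P than in group C". If both are met, the intervention is judged possibly useful.
- Protocol 11.1 bases the sample size on one calculation: "Assuming an effect size of 0.4, a significance level of less than 5% and a power of 0.8". It arrives at 52 in total, raised to 60 for enrolment, and does not mention that there are two endpoints.

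**The concern.** The test condition is singular and the direction condition covers every indicator, yet there are two endpoints and so two tests. At least three rules fit the text:

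1. *Either*: one endpoint is significant and that same endpoint is in the right direction.
2. *One p-value, both directions*: at least one endpoint is significant, and both have a higher mean in M or P than in C.
3. *Both*: each endpoint is significant and in the right direction.

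These rules differ in false-positive rate and, much more, in power. The single power figure in 11.1 cannot describe all three. A trial in which only one endpoint truly responds would very likely succeed under the first rule and almost never under the third. A reader of the result needs to know which rule was in force.

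**Working it through.** **Inputs.** Two endpoints (7.1); two-sided 0.05 (11.3); effect size 0.4, read as Cohen's f, and power 0.80 (11.1); 52 calculated and 60 planned, 20 per group (10 and 11.1); direction condition (11.3.2). The correlation between the endpoints is not given, so it is an assumption, varied from 0 to 0.8.

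**The protocol's own figure.** Power comes from the noncentral F distribution with noncentrality N × f² and N − 3 denominator df.
- 1 numerator df, N = 52: noncentrality 52 × 0.16 = 8.32, power 0.807. This reproduces 52.
- 2 numerator df, the three-group comparison in 11.3.2: power 0.707 at 52 and 0.776 at 60; 64 would be needed for 0.80.

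So one endpoint has about 78% power at 60 before multiplicity enters.

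**False positives, p-values only.** Independent endpoints: 1 − 0.95² = 0.0975. Simulation (200,000 trials, 20 per group, F on 2 and 57 df) gives 9.7%, 9.5%, 9.2% and 8.0% at correlation 0, 0.3, 0.5 and 0.8.

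**False positives under the written rule.** With no effect the three groups are exchangeable, so C has the highest mean one time in three, whatever the size of F. The direction condition therefore keeps two thirds of the significant results.
- One endpoint: 0.05 × 2/3 = 0.033.
- *Either*, independent: 1 − (1 − 0.0333)² = 0.066.
- *One p-value, both directions*, independent: 0.0975 × (2/3)² = 0.043.
- *Both*, independent: 0.0333² = 0.001.

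**Power when both endpoints respond, *both* required.** At N = 60 with 2 df and independence: 0.7757² = 0.60. A bivariate normal calculation gives 0.63, 0.65 and 0.70 at correlation 0.3, 0.5 and 0.8, and simulation agrees.

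**Power when only one responds**, independent endpoints.
- *Either*: 1 − (1 − 0.776)(1 − 0.033) = 0.78.
- *One p-value, both directions*: about 0.776 × 2/3 = 0.52, rising with correlation to between 0.58 and 0.60.
- *Both*: 0.776 × 0.033 = 0.026.

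**Summary over correlation 0 to 0.8** (60 analysed, f = 0.4 where an effect exists):

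| Reading | No effect: judged possibly useful | Both respond | Only one responds |
|---|---|---|---|
| Either | 5.4-6.6% | 86-95% | about 78% |
| One p-value, both directions | 4.4-5.3% | 86-95% | about 52-60% |
| Both | 0.1-1.3% | 60-70% | about 3% |

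**Sensitivity of the joint power.** From the nominal 0.80 per endpoint: 0.80² = 0.64, up to 0.73 at correlation 0.8. From the 1-df calculation at 60 (0.861 each): 0.74 to 0.81. With only 52 analysed and 2 df (0.707 each): 0.50 to 0.62.

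**The case against.** Four stronger conclusions might be inferred. The protocol does not support them.

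- *The false-positive rate is near 10%.* That is the chance of any p < 0.05. Section 11.3.2 also requires the right direction, which caps the error at about 6.6%, an excess of about 1.6 points over 5%.
- *No reading delivers the stated error and power.* A literal reading does so approximately. One p-value plus both directions has 4.4-5.3% error and 86-95% power when both endpoints respond, although power drops to about 52-60% when only one does.
- *The reading will be picked once results are known.* Section 11.3 requires an analysis plan before the first enrolment, and a change history if a second version is made. A post-hoc choice is therefore an assumption.
- *Flexibility should be the sole primary endpoint, because the fat pad is what is treated.* Section 5.3 does say the massage "will be performed on the infrapatellar fat pad for approximately 10 minutes", and the vibration goes to the same site. But section 1 sets the two aims side by side, and nothing ranks gliding as the less plausible target.

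It is also fair to say that the 60% power figure is the low end of its range, and that part of the shortfall belongs to the degrees of freedom in 11.1. All of this limits the size of the problem.

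The argument that multiplicity belongs in the unseen analysis plan carries less weight. The protocol itself fixes the level, the success rule and the power claim, and these do not fit together for two primary endpoints.

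**Conclusion.** The point holds in this limited form: there are two primary endpoints, one unadjusted 0.05 level, and a rule that leaves open whether one or both must be significant. The inflation of the error rate is modest. The larger consequence is for power, which is about 60-70% rather than 80% if both endpoints must be significant. Of that gap, the step from 80% to about 78% comes from the 2-df test and the rest from requiring two wins. When only one endpoint responds, the chance of success runs from about 3% to about 78% according to the reading.

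These figures assume 60 analysed, f = 0.4 on each responding endpoint, a three-group F test on 2 and 57 df, and an endpoint correlation between 0 and 0.8.

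**What to change.** - In 11.3.2, state that a win on either endpoint counts, and that the p-value and direction conditions apply to the same endpoint.
- In 11.3 and 11.3.2, apply Holm across the two endpoints at an overall two-sided 0.05: the smaller p-value is tested at 0.025 and, if it passes, the larger at 0.05. By the Bonferroni bound, the chance of any false rejection is at most 2 × 0.025 = 0.05 when neither endpoint responds, before the direction condition lowers it further.
- In 11.1, restate the power for this rule at the planned 60, using the 2-df three-group test.

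The cost is wording, plus some power. At 0.025 with 60 subjects, power for a single responding endpoint is about 68% instead of about 78%. If both respond and are independent, the chance of at least one win is 1 − (1 − 0.678)² = 0.90; correlation lowers this towards 68%. No added enrolment is needed if the figure is simply restated. If the team wants 80% power for each endpoint at 0.025, the 2-df test needs 76 subjects.
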